### Safety

2.6

The likelihood of serious adverse events (SAEs) occurring due to treatment is low since neither CBT-I nor sleep hygiene advice have been reported to cause them. We define SAEs as any untoward medical occurrence that either: (a) results in death, (b) is life- threatening, (c) requires inpatient hospitalisation or prolongation of existing hospitalisation, (d) results in persistent or significant disability/incapacity or (d) consists of a congenital anomaly or birth defect. Participants are asked for adverse events in the t1- and t2-visit and are further encouraged to inform the investigator at any time if any adverse event occurs. During the intervention period of the clinical trial, a monitor will review the study at least three times. Further visits will be added, if any deviations occur.

### Measures

2.7

In addition to demographic measures (age, gender, education, comorbidities, sleep environment, duration of illness), data on the primary and secondary outcomes is raised through questionnaires. An overview is given in Table 2.

**Table 2 T2:** Outcome measures.

	Outcome parameter	Questionnaire	Author
Primary endpoint	Insomnia severity	Insomnia Severity Index (ISI)	(46)
Secondary endpoints	Depressive symptoms	Patient Health Questionnaire-9 (PHQ-9)	(47)
	Anxiety symptoms	Generalized Anxiety Disorder (GAD-7)	(48)
	Daytime sleepiness	Stanford Sleepiness Scale (SSS)	(49)
	Health-related quality of life	Health-related quality of life in children and adolescents (KINDL)	(50)

#### Primary endpoint: insomnia severity

2.7.1

The German translation of the Insomnia Severity Index (ISI), a 7-item questionnaire, is used because of its good psychometric properties, as a high construct validity (correlation with Pittsburgh Sleep Quality Index; PSQI r = 0.79) and high reliability (test-retest analysis r = 0.78). It is recommended using the ISI as a screening tool in research and it is adequately quantifying changes during insomnia therapy (46). The use of the ISI is approved by MapiTrust and the translation was supervised by ICON.

For the primary outcome (i.e., insomnia severity) a responder analysis of the Minimal Clinically Important Difference (MCID) for the Insomnia Severity Index [change in the ISI-score of ≥8 (51);] is performed. This is examined for group differences.

#### Secondary endpoints

2.7.2

Measuring depressive symptoms, the Patient Health Questionnaire 9 (PHQ-9) is widely used and well validated. It is used here for its ability to detect changes in depressive symptoms over time (47). The Generalized Anxiety Disorder (GAD-7) is a short self-report questionnaire on symptoms of anxiety. Evidence from measuring subjects of the general population support validity and reliability of this instrument (48). For measuring subjective changes in daytime sleepiness, the Stanford Sleepiness Scale (SSS) is commonly used. It was shown to be sensitive to discrete changes in sleepiness and correlated with objective measures of vigilance (49). While originally validated in adults, the SSS has also been applied in research involving adolescents, including studies assessing sleepiness in school-aged populations and clinical trial contexts (52, 53). Its brief, momentary assessment format makes it feasible for repeated measurements in digital interventions targeting adolescents. Finally, for measuring the generic quality of life, the questionnaire “Health-related quality of life in children and adolescents” (Fragebogen zur Erfassung der gesundheitsbezogenen Lebensqualität bei Kindern und Jugendlichen; KINDL) is used. Results of psychometric testing of children with chronic illness and matched healthy children showed that the German KINDL is a practical, valid and reliable instrument (50).

#### Exploratory analysis

2.7.3

Exploratory analysis is performed to assess the number of adverse events (AE) in both groups. We will compare the number of specified adverse events between the groups descriptively by reporting these by randomised group. Since school-related and seasonal variations (e.g., school days vs. weekends, holiday periods) are controlled for by randomization to account for such systematic errors, and the randomization procedure ensures that no more than 2–4 participants are assigned consecutively to either group, larger block formations are excluded. To avoid confounding or account for it appropriately, we will analyze whether the holiday status systematically differs between groups at the 6- and 12-week-post-randomization-assessments. If such a difference exists, a sensitivity analysis should be considered.

As part of the sleep diary, participants of the IG are asked to fill out details about their daytime activity (incl. caffeine or alcohol consumption) and their sleep behavior (time in bed, time they fell asleep) throughout the entire intervention by using the diary function of the application. This data will be analyzed exploratively with regard to sleep efficiency, total sleep time, time in bed, sleep latency, and wake-time after sleep onset in the IG only. Further, duration and frequency of application-usage will be analyzed. A brief semi-structured interview will be conducted with all intervention-group participants at the post-intervention visit (week 12) to assess their attitude towards the digital intervention and to monitor participant adherence and engagement. Interviews will be audio-recorded and transcribed verbatim. Data will be analyzed using reflexive thematic analysis following Braun & Clarke's established phases (familiarization, coding, theme development, refinement, and reporting). Two trained researchers will independently code transcripts, meet to consolidate the coding framework, and iteratively develop themes. Rigor will be ensured through independent coding, resolution of discrepancies via discussion, maintenance of coding logs and analytic memos, and regular peer debriefing. The qualitative findings will contextualize user experiences with the digital intervention. The measures participants have taken for improving their sleep will be analyzed on group differences using a poisson model. Finally, strategies for improving sleep in both groups will be collected and analyzed.

### Statistical analysis

2.8

The primary statistical analysis will follow the intention-to-treat (ITT) principle. Efforts will be made to collect complete follow-up data for all participants to facilitate a comprehensive ITT analysis. However, missing data may occur due to withdrawals, loss to follow-up, or incomplete responses to some questionnaire items. Trial results will be presented as comparative summary statistics with 95% confidence intervals (CIs), and all tests will use a two-sided significance level of 5%. The study results will be reported in accordance with the Consolidated Standards of Reporting Trials (CONSORT) guidelines (54). A mixed effect linear model based on an unstructured covariance matrix will be fitted to the primary outcome data (ISI at 12 weeks), utilising 6- and 12-week timepoints. Participant will be included as random effects. Fixed effects will include randomized group, baseline ISI score, group, time and a time by randomized group interaction term to allow estimation of treatment effect at each timepoint. Missing data will be reported, including any available reasons for the missingness, and the patterns of missing data will be examined. The mixed-effects model inherently accounts for data assumed to be missing at random. Standard residual diagnostics will be conducted to evaluate the model's suitability. If the assumptions are found to be violated, alternative non-parametric methods will be considered for the primary analysis. Continuous secondary outcomes with only two time point measures (baseline and 12-weeks) will be analyzed with ANCOVA models, adjusting for baseline variable. The estimated difference between the groups after 12 weeks will be derived using a linear contrast statement from the ANCOVA model. Missing data, assuming confirmation of the “Missing at Random” (MAR) condition, will be estimated using multiple imputation. Subgroup analyses will be conducted based on gender (female, male). Secondary count outcomes (e.g., number of responders, number of side effects, number of measures to improve sleep) will be analyzed using Chi-Square tests. For the primary outcome, insomnia severity, a responder analysis will be conducted based on the Minimal Clinically Important Difference (MCID) for the Insomnia Severity Index (ISI), defined as a change in ISI ≥ 8. This analysis will examine differences between groups. Similarly, responder analyses will be conducted for depression [change in PHQ-9 ≥ 5 (47);] and anxiety measures [change in GAD-7 ≥ 3 (55);]. All outcomes were prespecified and are known to be correlated; therefore, consistent with methodological recommendations (56–58), no formal multiplicity adjustment will be applied.

The primary outcome measure is insomnia severity 12 weeks post-randomization. Assuming that this outcome follows a normally distributed population and that linear mixed models rely on pairwise comparisons, the hypothesis will be tested using a two-sided t-test for independent samples within a parallel-group design. To detect a statistically significant group difference with a Standardized Mean Difference (SMD) of 1.07 [the lower confidence interval of the within-group effect size reported in a prior study on the efficacy of digital CBT-I in adolescents using the Insomnia Severity Index (59);] with a power of 95% and an alpha level of 0.05, 24 participants per group are required [calculated using G*Power (60);]. Considering an anticipated dropout rate of 27% [based on (59)], a total of 66 adolescents should be randomized for the study.

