**Methods:**

This trial is a monocentric, national, prospective randomized controlled trial aiming to recruit 66 adolescent participants (14–17 years) meeting criteria for insomnia disorder in Germany. Participants will be randomized (1:1) to either 12 weeks of digital CBT-I (*somnio junior)* or sleep hygiene advice. Outcomes will be collected at baseline, 6- and 12-weeks post-randomization. The primary endpoint is self-reported insomnia severity using the Insomnia Severity Index at 12 weeks. Secondary endpoints include symptoms of depression, anxiety, daytime sleepiness and health-related quality of life. Analyzes will be intention-to-treat.

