**Figure 1 F1:**
[figure not shown]
Trial flow.

The study center is the Institute of Child and Adolescent Psychiatry at the Center for Integrative Psychiatry, School of Medicine in Kiel. The clinical trial is conducted entirely online. All visits and interviews are held via the video conferencing platform BigBlueButton (BBB) hosted by the Universitýs Computing Center and questionnaires are filled out online directly via the Electronic-Data-Capture-System (EDC). For instant technical support if required, participants are asked to fill out the questionnaires in the EDC, while staying in the online conference room. To ensure privacy, both, participants and investigators will turn off their camera and are muted.

The study protocol was registered in the German Clinical Trials Register (Deutsche Register Klinischer Studien; DRKS) (DRKS00033527; registration date 25.07.2024), approved by the Ethics Committee (Faculty of Medicine at the University of Kiel, 16.07.2024) and authorized by the German Federal Institute for Drugs and Medical Devices (BfArM, 04.10.2024). A SPIRIT-Checklist (Additional File S1) is provided (42).

A central gender-stratified block randomization with variable block size (2–4) is selected as the randomization procedure. This way, participants are equally distributed between IG and CG regarding gender, being the only stratification variable. Randomization will be implemented through the EDC by external staff of the Center of Clinical Trials (Zentrum für Klinische Studien; ZKS) in Kiel and the allocation sequence is concealed from the research team until interventions are assigned. After completion of the baseline assessment, allocation details will be communicated to participants by members of the research team. As this is an open-label study, both participants and research team members will be aware of the group assignments. The participant information sheet will explain that the study is comparing two sleep intervention programs but will not disclose the study hypothesis. Participants will complete outcomes remotely and without the presence of an investigator, although research staff monitor outcome ratings to assist in case of technical problems. Although blinding the research team is not feasible, the trial statisticians will remain blinded to group assignments.

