### Participants

2.4

We aim to recruit participants aged 14–17 years nationwide through flyers (containing study contact details) in regular care practices, clinics and through online advertisement in social media. Flyers and online advertisement link to the study homepage, which contains all information about the study. Since insomnia is more prevalent in female than in male adolescents [f:m = 3:1 (45)], we expect a similar gender distribution in our study sample.

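### Gender is the only stratification factor but is missing from the listed primary model and ANCOVAs; if gender is prognostic, the reported standard errors are modestly too large

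*Protocol article*

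**What the plan says.** Section 2.1 (Study design and setting) fixes the allocation method: "A central gender-stratified block randomization with variable block size (2–4) is selected as the randomization procedure". It goes on: "This way, participants are equally distributed between IG and CG regarding gender, being the only stratification variable". The abstract gives the ratio as 1:1.

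Section 2.8 (Statistical analysis) lists the terms of the primary model for the ISI at 6 and 12 weeks: "Fixed effects will include randomized group, baseline ISI score, group, time and a time by randomized group interaction term". Continuous secondary outcomes measured only at baseline and 12 weeks "will be analyzed with ANCOVA models, adjusting for baseline variable". Gender enters the analysis only as a subgroup factor.

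Sections 2.2 and 2.4.1 explain why usual care, comorbidities, medication and therapy are not covariates: randomisation is expected to balance them. No such reason, or any other, is given for gender.

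**The concern.** The allocation is restricted by gender, and the listed models ignore that restriction. Forced balance on a prognostic factor removes its variation from the comparison between arms. A model without the factor leaves the same variation in the residual, so the reported standard error exceeds the real sampling variability. Confidence intervals are then too wide and p-values too large. For the same reason, the argument from balance used for the other variables would not justify leaving out a stratification factor.

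The article spells out its fixed effects, so this is a stated choice and not detail left to a statistical analysis plan. What is at stake is the reported precision for the primary outcome and the continuous secondary outcomes, in a trial planned around 48 completers.

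**Working it through.** **Inputs from the protocol article.** SMD 1.07, two-sided alpha 0.05, power 95%, 24 per group, dropout 27%, 66 randomised (section 2.8); expected female-to-male ratio 3:1, so p = 0.75 (section 2.4); 1:1 allocation (abstract).

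**Assumed input.** d is the female-male difference in the 12-week outcome after baseline adjustment, in residual SDs. The article gives no value, so a range including zero is used.

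**The plan's own figure.** A two-sided two-sample t-test with the noncentral t distribution at SMD 1.07 gives power 94.4% with 23 per group and 95.2% with 24. So 24 is the minimum. For dropout, 48 / 0.73 = 65.8, rounded up to 66. The stated sample size reproduces, and nothing below changes it.

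**Standard error excess.** With arms balanced within gender, omitting gender adds p(1 − p)d² to a residual variance of 1, so

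SE ratio = √(1 + p(1 − p)d²), with p(1 − p) = 0.75 × 0.25 = 0.1875.

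For example, at d = 0.5: √(1 + 0.1875 × 0.25) = √1.0469 = 1.023. At d = 0.8: √(1 + 0.1875 × 0.64) = √1.12 = 1.058.

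**Simulation.** 66 participants, gender-stratified blocks of 2 or 4, ANCOVA at one time point with and without gender, residual SD about 1, 6,000 runs per setting, with no dropout and with 27% random dropout.

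| d | Residual variance due to gender | SE excess, formula | SE excess, simulated, 27% dropout | Power at 1.07, 27% dropout: without / with gender |
|---|---|---|---|---|
| 0 | 0% | 0% | −0.4% | 94.3% / 94.2% |
| 0.3 | 1.7% | 0.8% | 0.5% | 93.9% / 93.9% |
| 0.5 | 4.5% | 2.3% | 2.0% | 93.8% / 94.4% |
| 0.8 | 10.7% | 5.8% | 5.5% | 92.7% / 94.3% |
| 1.0 | 15.8% | 9.0% | not run | not run |

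The −0.4% at d = 0 is the price of the extra term when gender does not matter.

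**Reported against real variability.** At d = 0.8 without dropout and with no treatment effect, the empirical SD of the treatment estimate is 0.246 whether or not gender is in the model. The mean model SE is 0.262 without gender and 0.247 with it, a ratio of 1.059. Only the reported SE differs. With 27% dropout, balance is no longer exact: at d = 0.8 and SMD 1.07 the empirical SD is 0.296 without gender and 0.290 with it, so adjustment also recovers about 2%. The estimate shows no material bias in any setting.

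**Type I error without gender.** With no dropout it is 4.6% at d = 0.5 and 3.7% at d = 0.8. With 27% dropout it is 4.5% and 4.6%. The Monte Carlo standard error is √(0.05 × 0.95 / 6000) = 0.28 points, so the conservatism under dropout is slight.

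**If the true effect is smaller.** At an assumed SMD of 0.6 with 27% dropout, power without and with gender is 50.4% and 52.2% at d = 0.5, and 46.7% and 51.0% at d = 0.8.

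**The case against.** The strongest objection is that the article nowhere says gender is prognostic. Its figures by gender are prevalences (23.6% against 12.5% in section 1; 3:1 in section 2.4). Everyone enrolled has diagnosed insomnia and the primary model already adjusts for baseline ISI, so prevalence does not tell us whether gender predicts the 12-week score. With d = 0 nothing is overstated. This stands, and it is why the point is conditional.

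A reader might infer several stronger things that the documents do not support:

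- **That the planned intervals and p-values are simply wrong.** They are too wide only if gender is prognostic, and by about 2% or less for d up to 0.5 under the planned dropout.
- **That the precision gained by stratifying is lost.** The estimate keeps it; the reported standard error fails to show it.
- **That conservatism is marked.** A calculation with exact gender balance among 48 completers would suggest so, but stratification balances the 66 randomised, and dropout weakens that balance.
- **That the second mention of group was meant to be gender.** This is possible but cannot be shown, and it would not repair the ANCOVAs.
- **That the same covariate should be added to the responder analyses.** Section 2.8 compares responders by chi-square tests, so there is no model to which a term could be added.

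The form of the gender subgroup analysis, and its power in boys, is ordinary analysis-plan detail and has no bearing on the omitted covariate.

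**Conclusion.** The point holds in a limited form. The one factor used to stratify randomisation is absent from both stated models, and the primary model's list contains a repeated term that needs correcting in any case. The consequence is conditional and runs in the conservative direction: a standard error excess from nil to about 6% for d between 0 and 0.8, and 9% at d = 1.0, with a power loss at the design effect of at most about 1.6 points for d up to 0.8. The loss becomes more noticeable, about 4 points, only if the true effect is well below 1.07 and gender is strongly prognostic.

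These figures rest on an assumed d, a 3:1 gender mix, dropout at random, and a single-time-point ANCOVA standing in for the two-time-point mixed model. The validity of the treatment comparison is not threatened. This is a worthwhile, inexpensive improvement, best made while the trial is still recruiting (section 3.3), because adding the covariate once results are known would look post hoc.

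**What to change.** In section 2.8, add gender as a fixed effect to the primary mixed model and to each secondary ANCOVA, and replace the repeated group term so that each effect is named once. If the second mention was meant to be another variable, state which.

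The cost is one degree of freedom per model. Gender is already collected for stratification, and the sample size of 66 does not change. If gender turns out not to be prognostic, the price is an increase of about 0.4% in the standard error.

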At 6- and 12-weeks post-randomization, the midpoint and post visits are conducted via BBB as well. To reduce bias due to the investigator knowing the group allocation, a standardized interview protocol is provided for the midpoint- and post-visit (Additional Files S5, S6). Investigators are instructed to strictly follow the protocol. While educating on study-specific information and screening for eligibility is done by a physician, psychologists will conduct the baseline assessment, initiates the randomization process and conduct midpoint and post visits. At the midpoint and post visits, investigators have knowledge of both baseline clinical information and allocation status. During these visits, adverse events are inquired. These also comprise worsening of e.g., affective symptoms. Further, changes in medication or psychotherapy and the periods during which school holidays took place are recorded. Questionnaires are filled out by the participants directly via the EDC (SecuTrial). At the post visit, after participants have filled out the t2-questionnaires, participants are asked an open-ended question about any additional strategies they used to improve their sleep outside the study intervention; responses will be categorized and summarized using descriptive frequency counts. Further, a semi-structured interview is conducted with participants of the IG to assess their attitude towards the digital intervention and to monitor participant adherence and engagement. The medical report is discussed to evaluate the individual development of different sleep-related parameters. All source data (e.g., protocols of visits, etc.) are digitalized and saved in pseudonymized form. Participants are financially compensated for their time by a 30€ voucher (10€ for each t0, t1 and t2 assessment).

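### The number of sleep measures is given a Chi-Square test in 2.8 and a Poisson model in 2.7.3, and side effects get a Chi-Square test with no unit stated

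*Protocol article*

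**What the plan says.** Section 2.8 (Statistical analysis) groups three quantities under one test: "Secondary count outcomes (e.g., number of responders, number of side effects, number of measures to improve sleep) will be analyzed using Chi-Square tests". It also states that "all tests will use a two-sided significance level of 5" per cent, and it plans no multiplicity adjustment.

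Section 2.7.3 (Exploratory analysis) covers two of the three differently:

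- Sleep measures: "The measures participants have taken for improving their sleep will be analyzed on group differences using a poisson model".
- Adverse events: "Exploratory analysis is performed to assess the number of adverse events (AE) in both groups", and then "We will compare the number of specified adverse events between the groups descriptively by reporting these by randomised group".

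Section 2.5 (Procedure) describes an open-ended question at the post visit on other strategies used to improve sleep, for which "responses will be categorized and summarized using descriptive frequency counts".

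Section 2.6 (Safety) describes how events are gathered: "Participants are asked for adverse events in the t1- and t2-visit and are further encouraged to inform the investigator at any time".

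Table 2 lists neither side effects nor sleep measures among the primary and secondary endpoints.

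**The concern.** There are two problems.

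First, the sleep-measures comparison has two inferential methods and two labels (secondary in 2.8, exploratory in 2.7.3), with no rule for choosing between them. With two prespecified tests, the choice of which to report could follow the result. The comparison has some weight in interpretation: the trial is open-label, its Limitations section concedes unequal engagement and contact between arms, and different use of outside strategies would bear on how an ISI difference is read.

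Second, 2.8 itself calls these outcomes counts. Events are asked about at two visits and can be reported at any time, and an open-ended question can draw several answers, so one participant can contribute more than one. A Chi-Square test suits a yes/no status per participant, such as response. It does not suit a count that can exceed one, and 2.8 does not say that counts are first reduced to yes/no.

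**Working it through.** **The texts side by side**

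| Outcome | 2.8 | 2.7.3 | 2.5 |
|---|---|---|---|
| Sleep measures | secondary, Chi-Square | exploratory, Poisson model | categorized, frequency counts |
| Side effects / adverse events | secondary, Chi-Square | exploratory, descriptive by arm | – |
| Responders | secondary, Chi-Square | – | – |

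The first row holds two different tests of one comparison. The frequency counts in 2.5 can stand beside either. In the second row the status differs, and a test appears in one place only.

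**Arm sizes**

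The document gives no figure for the count outcomes, so only its sample size can be reproduced. For "To detect a statistically significant group difference with a Standardized Mean Difference (SMD) of 1.07", two-sided 5%, the noncentral t gives power 0.944 at 23 and 0.952 at 24 per group, hence 24. With 27% dropout, 48 / 0.73 = 65.8, hence 66, or 33 per arm. Both stated figures reproduce. The checks below use 24 and 33 per arm.

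**Reading A: Chi-Square on event totals**

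Let S1 and S2 be the event totals in two equal arms of n participants. Each expected total is (S1 + S2)/2, so

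X² = (S1 − S2)² / (S1 + S2).

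If each participant's count has mean μ and variance φμ, then with no true difference Var(S1 − S2) = 2nφμ, while S1 + S2 averages 2nμ. X² therefore behaves like φ times a 1-df chi-square, and

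type I error ≈ 2 × [1 − Φ(1.96 / √φ)].

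The document gives neither μ nor φ; both are assumptions. The simulation used negative binomial counts (Poisson at φ = 1), μ = 1, 2 and 3, 24 and 33 per arm, and 20,000 runs per setting.

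| φ (assumed) | 1.96/√φ | Formula | Simulated range |
|---|---|---|---|
| 1 | 1.960 | 5.0% | 4.6–5.1% |
| 1.5 | 1.600 | 11.0% | 10.8–11.3% |
| 2 | 1.386 | 16.6% | 16.3–16.7% |
| 3 | 1.132 | 25.8% | 25.3–26.2% |

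A Poisson model whose standard error is scaled by the estimated dispersion stayed at 4.5–5.2% throughout. A plain Poisson model does not: with equal exposure its score statistic is the same X².

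**Reading B: Chi-Square on a table of count levels (0, 1, 2, …)**

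The participant is the unit, but order is ignored. Power was simulated with Poisson counts (φ = 1) and assumed means:

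| Per arm | Means | Count-level table | Any v none | Poisson rate test |
|---|---|---|---|---|
| 33 | 2 v 3 | 29% | 24% | 72% |
| 33 | 1 v 1.75 | 36% | 43% | 72% |
| 24 | 2 v 3 | 18% | – | 59% |

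Hand check of the first row: ln(3/2) / √(1/66 + 1/99) = 0.405 / 0.159 = 2.55, and Φ(2.55 − 1.96) = 0.72. At 33 per arm, about 59% (2 v 3) and 46% (1 v 1.75) of the cells in the count-level table have expected counts below 5.

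**Reading C: Chi-Square on any v none**

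This is valid, with type I error of 5–6% across the dispersions tried, but it discards the size of the count (power in the table above).

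Readings A and B do not add up. A inflates error under overdispersion and loses no power to the Poisson test (about 60% at 24 per arm, means 2 v 3). B loses power. No single reading produces both harms.

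**The case against.** The strongest defence is that 2.8 never says the counts are per participant. Its first example, responders, is a number of people per arm. If side effects are read the same way, as participants affected, Chi-Square is valid. That stands as a possible reading, but the text does not state it, and it would not reconcile Chi-Square with Poisson for sleep measures.

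Several stronger inferences are tempting and not supported:

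- **Three incompatible methods for sleep measures.** The frequency counts in 2.5 are a summary and exclude no test. The conflict is Chi-Square against Poisson.
- **Adverse-event statements that cannot both be followed.** Section 2.7.3 says the comparison is descriptive; it does not rule out a test as well. Nor does the document define side effects and adverse events as the same set, although adverse events are the only ones whose collection it describes. The conflict in status and the missing unit stand; strict incompatibility does not.
- **A safety comparison known to be inflated.** The 11–26% rests on assumed overdispersion and on Reading A. It applies equally to a plain Poisson model, so 2.7.3 as worded is no cure.
- **Opposite answers from the two sections.** The calculation shows different power, not a reversed direction.
- **A wrong test for responders.** An unadjusted Chi-Square on a binary outcome is valid under randomization. Adjusting for baseline is a matter of efficiency, not the correction of an error.

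**Conclusion.** The point holds in limited form. The Chi-Square/Poisson conflict for sleep measures is on the face of the text and needs no assumption. The difference in status and the unstated unit for side effects are real but softer. Chi-Square does not suit a count that can exceed one per participant, unless that count is first reduced to yes/no.

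The size of the harm is conditional: no inflation at variance/mean 1, about 11%, 17% and 26% at 1.5, 2 and 3 if event totals are tested, and a marked loss of power if count levels are tabulated. These figures illustrate assumed counts and do not predict this trial's data.

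Severity is minor to moderate. Both outcomes lie outside Table 2, no stated decision rule uses them, and the primary ISI analysis and the sample size are untouched.

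**What to change.** - **2.8:** remove side effects and sleep measures from the Chi-Square sentence. Keep Chi-Square for responders.
- **Sleep measures (2.7.3 and 2.8):** name one count model that allows overdispersion, either negative binomial or Poisson with robust or scaled standard errors. Keep the frequency counts in 2.5 and say that they are a descriptive summary.
- **Adverse events (2.7.3 and 2.8):** use one term, or define side effects separately. Report by arm both the number of events and the number of participants with at least one event, and base any test or interval on participants.
- **Status:** label each outcome secondary or exploratory, identically in 2.7.3 and 2.8.

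The cost is a few sentences and trivial analysis work. No data collection changes. The trial is still recruiting, so the edit can be dated before the trial statisticians, who are to stay blinded to group, see results by arm.
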